##### Statistical criteria for termination of trial

No early stopping is planned, either for efficacy or for futility.

### Quality assurance and control

The principle investigator (PI) is responsible for implementing and maintaining quality assurance and quality control systems with written SOPs and Working Instructions. The PI is responsible for proper training of all involved study personnel. To assess high-quality conduct of the trial in accordance with the protocol, all medical staff involved in this study are certified in good clinical practice (GCP).

#### Data handling and record-keeping/archiving

Paper documents including the results of the blood analysis, the headache diaries, questionnaires and all study-related documents will be filed in the study files and stored in the hardcopy archive of UKBB on a dedicated shelf.

#### Case report forms

For each subject included in this study, a case report form (CRF) will be completed, dated and signed by a study investigator. Data will be recorded in the CRF from the source documents, which may include medical notes and results obtained from laboratory reporting systems.

All participants receive a unique identification number (patient ID) and no identifying data such as name, initials or birth date will be collected in the CRF.

#### Specification of source documents

Source data will be available at the site to document the existence of the study participants. Source data will include the original documents relating to the study (patient demographics, medical history, medication, neurological examination, informed consent forms) as well as the MIDAS and the HIT-6 questionnaire.

#### Record-keeping/archiving

All study data, including CRFs and informed consent forms, will be archived for a minimum of 10 years after termination (or premature termination) of the clinical research project. Paper documents including the results of the blood analysis and gene expression changes as well as questionnaires will be stored in the hardcopy archive of the UKBB.

#### Monitoring

To ensure the quality of the study conduct and of the data, monitoring of the study will be performed by a person independent of the study (Kammermann Monitoring Services GmbH, Zug, Switzerland). All inclusion and exclusion criteria will be checked and whether the data have been recorded correctly in the CRF, whether the drug accountability is correct and whether SAEs have occurred during the study.

#### Audits and inspections

All study documentation and the source data/documents will be accessible to auditors/inspectors (also EKNZ and CA) and questions will be answered during inspections. All involved parties must keep the participant data strictly confidential.

#### Confidentiality and data protection

Direct access to source documents will be permitted for purposes of audits and inspections (ICHE6, 6.10). The investigators of the study will have access to the protocol, dataset (including questionnaires, demographical/clinical data) and statistical code during and after the study. The patients’ identities will never be published in any abstracts or publications. A transfer of data will only take place for study purposes and only in encoded form. Third persons will not gain any insight into original data. For inspection purposes, insight into the original data will be permitted to the members of the appropriate authorities and also for the members of the local ethics committee, EKNZ. During the study, confidentiality will be guaranteed. The principal investigator will guarantee compliance with national and international data security.

#### Storage of biological material, related health data and returned study medication

Blood samples will be sent immediately to the earlier specified research laboratories. DNA and RNA extraction will be conducted immediately after arrival at the research laboratory. The extracted DNA/RNA will be sent for microarrays analysis on dry ice to Life&Brain, Bonn, Germany.

Biological material and related health data will be stored in an encrypted format for follow-up analyses.

In order to assess compliance of study medication intake, empty and full sachets are returned by the patients at visits 3, 4, 6 and 7. A member of the study team will count and balance the returned containers and can check the correct intake. This will be captured in an appropriate form. A qualified person from the study team will check the number of dispensed/taken medications and complete a study-specific drug accountability form. After completion of the clinical trial, leftover study medication will be destroyed.

### Safety assessments

Adverse events are monitored throughout the study. At every study visit, patients are asked about adverse events and their vital parameters are measured. If an AE is reported, a clinical examination is performed. The following safety parameters amongst other parameters are checked at visits 2, 3, 4, 5, 6 and 7 to determine safety of the treatment: routine laboratory parameters (renal and liver function tests, electrolytes, full blood count, C-reactive protein, serum cholesterol, triglycerides, serum proteins, albumin, glucose, Hba1c, insulin, cortisol, lactate, TSH, FT4 and FT3), blood pressure, heart rate, weight and height, assessed after 5 min of resting in a supine position.

As βHB is an endogenous substance we are not expecting any treatment-related serious adverse events on routine laboratory measures. Nevertheless, the intake of the IMPs will be stopped in the case of clinically significant changes in any of the parameters measured. In the event of any serious adverse events (treatment related or unrelated) occurring during intake of the IMPs, treatment will also be stopped immediately. If pathologic changes should be detected, whether related to or independent of migraine, the affected patients will be informed immediately and the possibilities of further investigation, respectively treatment of these abnormalities according to current medical knowledge, will be discussed.

#### Reporting of serious adverse events and other safety-related events

Treatment-emergent serious adverse events (any event regardless of potential causality with the drug) and treatment-related adverse events as imputed by the principal investigator (such as gastrointestinal upset) will be recorded. Reporting to the EKNZ will take place according to the clinical trials of medicinal products guidelines for notification and reporting of Swissethics. In brief:Serious adverse events (SAEs) with fatal consequences or where a connection is suspected with the intervention will be reported within 7 days.Suspected unexpected serious adverse reactions (SUSARs) with fatal consequences will be reported within 7 days, other SUSARs within 15 days.SAEs that may be related to the intervention under investigation in other clinical trials will be reported within 15 days.

AEs of this trial are graded in the most recent Common Terminology Criteria for Adverse Events (CTCAE) version 5.0, which was published in November 2017 and became effective in April 2018 [66], published by the National Cancer Institute (NCI) of the National Institutes of Health (NIH).

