### Safety outcomes measures

Safety and tolerability will be determined by:comparison of treatment-emergent adverse events (any event regardless of potential causality with the drug) and treatment-related adverse events (such as gastrointestinal upset) as imputed by the principal investigator between active treatment and placebo; andexamination for potential effects of the intervention on routine laboratory parameters (renal and liver function tests, electrolytes, full blood count, lipids, glucose, CRP, Hba1c, insulin, cortisol, lactate, TSH, FT4 and FT3) in the treatment group compared to the control group.

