**Fig. 2 Fig2:**
[figure not shown]
Detailed study schedule. ^1^Blood pressure, heart rate, weight and height. ^2^Pen and paper headache dairy. ^3^Migraine Disability Questionnaire (Migraine Disability Assessment (MIDAS)) and Headache Impact Test (HIT), German versions, standard questionnaires for assessing the extent of migraine-related disability. ^4^Blood beta-hydroxybutyrate and glucose levels, measured with a portable ketone meter (precision xtra by Abbot). ^5^Routine laboratory (renal and liver function tests, electrolytes, full blood count, C-reactive protein, serum cholesterol, triglycerides, serum proteins, albumin, glucose, Hba1c, insulin, cortisol, lactate, TSH, FT4 and FT4). ^6^Blood draw (1 × EDTA, 1 × PAXgene) at each time point for genetic profiling and gene expression analysis using microarrays. ^7^Blood draw at each time point for oxidative and nitrosative stress markers (malondialdehyde (MDA), carbonylated proteins, nitrite, nitrotyrosine) and serum cytokine measurements (including, but not limited to, IFN-γ, IL-1β, IL-2, IL-4, IL-5, IL-6, IL-10, MCP-1, TNF-α, TNF-β, TGF-β1). V = visit

At the start of the intervention (baseline/V2, week 0) the following procedures are performed: check inclusion/exclusion criteria and, if met, confirmation of enrolment, migraine diary check, diet check, consumption of first dose of IMP/placebo, adverse events, vital signs, physical examination if necessary, blood draw (for safety, biomarkers and genetic analysis), standardised migraine questionnaires, KB and glucose concentration measurements using a portable point-of-care blood ketone meter (precision xtra from Abbot) and/or the Abbott FreeStyle Libre Blood Glucose Monitoring System. Patients will be randomly assigned to the treatment or control group and receive the according study medication, which will be consumed three times daily for the following 12 weeks. V2 takes approximately 60 min.

After 4 weeks of intervention, there will be another visit (V3, week 4), during which KB and glucose levels will be measured, adverse events will be recorded, vital signs, diet and migraine diary will be checked, a dose of IMP/placebo will be consumed, blood for safety will be drawn, physical examination will be performed if necessary, participants will be provided with the rest of the study medication for the first intervention period and sachets of used study medication will be collected for compliance control. V3 takes about 30 min.

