During the visit after the first intervention period (V4, week 12), the following procedures are performed: migraine questionnaires, migraine diary and diet check, consumption of IMP/placebo, KB and glucose measurements, vital signs, blood draw for biomarker and safety analysis, physical examination if necessary and sachets of used study medication will be collected for compliance control. V4 takes about 60 min.

After 8 weeks without intervention, V5 (week 20) takes place, which is identical to the baseline visit (V2). V5 includes the following procedures: standardised migraine questionnaires, migraine diary and diet check, consumption of IMP/placebo, blood draw for biomarker and safety analysis, physical examination if necessary, KB and glucose concentration and vital signs. At this visit the patients will receive the alternative treatment to the first intervention.

After 4 weeks of the second intervention, V6 (week 24, analogous to V3) takes place. The following procedures are performed: migraine diary and diet check, consumption of IMP/placebo, KB and glucose measurements, adverse effects, vital signs, blood draw for safety and physical examination, if necessary. Participants will be provided with the rest of the study medicament and sachets of used study medication will be collected for compliance control. V5 takes about 30 min.

After completion of the second intervention, the last visit (V7, week 32, analogous to V4) takes place. The following procedures are performed: migraine questionnaires, migraine diary and diet check, consumption of IMP/placebo, KB and glucose measurements, vital signs and blood draw for biomarker and safety analysis, physical examination if necessary and collection of sachets of used study medication for compliance control.

All investigations will take place at the clinical trial unit of the University Hospital Basel, Switzerland. Participants are required to keep a detailed headache diary for the entire duration of the study.

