##### Safety analysis

Safety and tolerability will be determined by:comparison of treatment-emergent adverse events (any event regardless of potential causality with the drug) and treatment-related adverse events as defined by the principal investigator between active treatment and placebo; andexamination for potential effects of the intervention on routine laboratory parameters (renal and liver function tests, electrolytes, full blood count, CRP, lipids, Hba1c, insulin, cortisol, lactate, TSH, FT4, FT3) in the treatment group compared to the control group.

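### The sentence stating which adverse events are recorded is narrower than the planned all-causality safety comparison: it leaves out non-serious events judged unrelated

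*Protocol article*

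**What the plan says.** Two places in the protocol article define the safety comparison. The section on safety outcome measures gives it as "comparison of treatment-emergent adverse events (any event regardless of potential causality with the drug) and treatment-related adverse events". The Safety analysis section repeats it: "comparison of treatment-emergent adverse events (any event regardless of potential causality with the drug) and treatment-related adverse events as defined by the principal investigator". Both contrast active treatment with placebo, and neither limits the first category to serious events.

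Under Safety assessments, the subsection on reporting serious adverse events and other safety-related events opens by naming what will be recorded: "Treatment-emergent serious adverse events (any event regardless of potential causality with the drug) and treatment-related adverse events as imputed by the principal investigator". Gastrointestinal upset is its example of a treatment-related event. The rules for reporting to the ethics committee come after this sentence.

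Three other statements bear on collection:

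- Safety assessments says "Adverse events are monitored throughout the study" and "At every study visit, patients are asked about adverse events and their vital parameters are measured".
- Study procedure says of V3 that "adverse events will be recorded, vital signs, diet and migraine diary will be checked", without reference to seriousness or cause.
- Study procedure lists for V4 "migraine questionnaires, migraine diary and diet check, consumption of IMP/placebo, KB and glucose measurements, vital signs, blood draw for biomarker and safety analysis", followed by physical examination if necessary and sachet collection. No adverse-event item appears there, nor in the corresponding list for V7.

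**The concern.** An all-causality comparison exists so that the result does not rest on anyone's opinion about cause. To deliver it, every treatment-emergent event has to reach the database, including the minor ones thought to have another explanation. The recording sentence uses almost the same formula as the two outcome statements but adds the word serious to the first category. The phrase about causality then applies to serious events alone, so for non-serious events the investigator's attribution decides whether they are named for recording at all.

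This matters more here than in many trials. Demonstrating safety is part of the stated aim in the Abstract. The section on the experimental intervention says that there appear to be no published human data on these two salts, so there is little basis for calling an event unrelated. The Discussion also accepts that adverse events can unmask treatment when a patient receives both products. Blinding therefore reduces the risk that attribution differs between products but does not remove it. An event left out at the visit cannot be recovered in the statistical analysis plan.

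**Working it through.** No calculation in the plan is at issue. The check sets the statements side by side.

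**Step 1: categories needed and categories named.** Adverse events under treatment fall into four cells, by seriousness and by the principal investigator's attribution.

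| Event | Needed for the planned comparison (safety outcomes; Safety analysis) | Named in the recording sentence |
|---|---|---|
| Serious, judged related | yes | yes |
| Serious, judged unrelated | yes | yes |
| Non-serious, judged related | yes | yes |
| Non-serious, judged unrelated | yes | **no** |

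Three of the four cells agree. The fourth is needed for the comparison but not named for recording.

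**Step 2: what the comparison becomes under the literal sentence.** The article plans two comparisons: all treatment-emergent events, and treatment-related events. If only the named categories are entered, the first set equals the second plus serious events judged unrelated. The all-causality comparison then adds little to the treatment-related one and rests largely on the same attribution.

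**Step 3: whether another statement settles the matter.** The general rule in Safety assessments covers monitoring and asking. It does not say which answers are entered. The V3 list does say that adverse events are recorded, with no limit. The article therefore holds an unrestricted recording statement for one visit and a narrower general one, and it does not say which governs.

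**Step 4: visit lists against the every-visit rule.**

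| Visit | Week | Adverse events in the procedure text |
|---|---|---|
| V2 | 0 | listed |
| V3 | 4 | listed, as recorded |
| V4 | 12 | not listed |
| V5 | 20 | not in its own list, but the visit is declared identical to V2 |
| V6 | 24 | listed, as adverse effects |
| V7 | 32 | not listed |

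Only V4 and V7 lack the item. The every-visit rule covers both, so these two lists are incomplete rather than evidence that the question is not asked.

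**The case against.** The strongest reply is that this is a drafting slip in a condensed article. The recording sentence does not say that other events are excluded. It stands under a heading about reporting and leads straight into ethics-committee notification. Its parenthesis repeats the outcome definition almost word for word, which suggests that the same definition was meant. The same subsection says that the trial's adverse events are graded by CTCAE, without limiting this to serious or related events, and grading presupposes a record. The V3 list and the every-visit rule point the same way. Detailed recording instructions may stand in the full protocol.

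Much of this stands. It makes full collection the likelier intention, and it rules out the claim that the article forbids recording the missing category. It does not remove the conflict. The heading extends to other safety-related events, and the sentence covers non-serious related events and speaks of recording before any reporting rule begins. It is the article's only general statement of which categories are recorded.

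A reader might go further on the visit lists. V3 is at week 4 and V4 at week 12, so one might infer that 12 − 4 = 8 of the 12 weeks in each treatment period pass without an adverse-event question by the end of treatment. The article does not support this. The every-visit rule includes V4 and V7, V5 takes over the V2 list, and the schedule in Fig. 2 is not shown and may carry the item.

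**Conclusion.** The conflict is real and confined to one category: non-serious treatment-emergent events that the principal investigator judges unrelated. They are needed for the comparison set out in the safety outcomes and Safety analysis sections, but the general recording sentence does not name them. If that sentence is followed literally, the all-causality comparison is incomplete and depends on attribution.

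The size cannot be quantified. The article gives neither expected adverse-event rates nor the share of non-serious events likely to be judged unrelated. The conclusion rests on a literal reading; if the site in practice enters every event, as the V3 list suggests, nothing is lost and only the wording is wrong.

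A reader might infer that the planned safety comparison cannot be made at all. That goes too far: three of the four categories are named, and other statements support collecting all four. The gaps in the V4 and V7 lists are a secondary inconsistency. The point is still worth correcting, because safety is a stated aim and unrecorded events cannot be restored later.

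**What to change.** In the subsection on reporting serious adverse events and other safety-related events, delete the word serious from the recording sentence. It then covers all treatment-emergent adverse events, serious or not and related or not, and agrees with the two statements of the safety comparison. The expedited-reporting rules that follow stay unchanged.

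As a secondary edit in Study procedure, add adverse events to the V4 and V7 lists so that they agree with the every-visit rule. V5 needs no change, because it is declared identical to V2.

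The cost is the wording change and a few more adverse-event entries at existing visits. No visit, sample size or analysis changes.

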#### Follow-up of (serious) adverse events

Patients with adverse reactions which have occurred in the context of the study will be followed up by the investigator up to 30 days after the last visit.

## Discussion

We propose a single-centre, randomised, double-blind, placebo-controlled, crossover trial to determine whether treatment with βHB in mineral salt form has a positive effect on migraine frequency and associated symptoms. To our knowledge this is the first RCT using exogenous KB salts worldwide. If proven effective, βHB might offer a new prophylactic treatment option for moderately to strongly affected migraine patients, or at least a subgroup thereof. A demonstration of its safety might additionally pave the way for clinical trials assessing its use in related diseases.

Planning clinical trials in migraine is challenging for the following reasons: migraine is an episodic disease with a fluctuating nature (i.e. in some patients, migraine frequency can vary substantially from one month to the next or one season to the other, which makes it harder to demonstrate a treatment-related effect); the placebo effect is quite large, between 20 and 40% [67], which further adds to this problem; individual migraine attacks are of different length, and in more severely affected patients are sometimes hard to identify [68]; some patients suffer from headache of a different quality in addition to migraine and this distinction must be made by the patient subjectively [68]; and there is no objective biomarker for migraine or disease severity [68].

In order to address these problems, we have: incorporated two baseline periods to account for seasonal changes, and chosen a conservative effect size as well as a study population of moderate to high-frequency episodic migraineurs (5–14 headache days per month), in order to make it easier to demonstrate a sufficiently large effect size within a short timeframe, without introducing any confounds associated with chronic migraine, such as frequent co-morbidities [69]; calculated with a quite large placebo effect of 30%; chosen migraine days versus migraine attack frequency as the primary outcome; included a thorough briefing of each patient on the characteristic features of a migraine versus a headache attack; and included a detailed medical history and diagnostic consultation by a neurologist, as well as a carefully constructed headache diary.

We have decided in favour of a crossover design in this single-centre RCT for the following reasons. Despite all efforts, recruitment has been slow and screening failures were a little higher than expected; in addition, we found that patients tended to be discouraged when they learned that they had solely a 50% chance of trying the IMP and would only find out which treatment arm they belonged to upon trial completion (in over 2 years time).

A crossover design in migraine is typically not recommended [68] because of the following limitations [67]: the possibility of a carry-over effect; the need for a long total period of treatment (extended by a wash-out period) with concomitant increases in drop-outs over time and in turn loss of statistical power [70]; and the increased likelihood of adverse events, which can unmask the blinding when a subject is exposed to both treatments.

In our case, a crossover design has three key advantages:A crossover design greatly improves statistical power, as each patient can be his/her own control (within-subject analysis versus between-subject analysis), which can be especially useful in a heterogeneous disease such as migraine, and hence fewer patients would be necessary to demonstrate a given effect. The sample size is effectively halved, even when more conservative a priori assumptions are employed, which is advantageous in single-centre studies. To compensate for some of the aforementioned weaknesses of crossover designs in migraine, we decided to make our a priori assumptions to determine the sample size more conservative than we would have with a parallel group design: a statistical power of 90% and a drop-out rate of 30% were chosen (in addition to a 30% placebo effect).A crossover design gives each patient the chance to try the IMP, which—from our experience—increases compliance, motivation and participation rates. We asked 25 prospective subjects for their preference and all of them favoured a crossover over a parallel group design. Instead of 6 months including a follow-up period, patients are now participating for a total of 9 months. The longer duration might lead to a slight increase in drop-out rates; however, on the other hand, it also leads to much improved participation rates, while only needing half of the patients. Additionally, it is known that vigilant patient education, monitoring and follow-up may reduce drop-out rates in longer trails [70]. From our experience, the moderate increase in trial duration has nowhere near negatively outweighed the positive impact of being guaranteed exposure to the IMP. A subsequent open-label period at the termination of the parallel group design would have a similar effect, but would also increase the costs substantially, as it does not have any impact on statistical power. This can be problematic, particularly for investigator-initiated trials.In addition to adding a wash-out period, the crossover design also allowed us to incorporate a second baseline period. This might help control for any potential seasonal effects on migraine frequency.

The possibility of a carry-over effect is always there; however, with a very short half-life of approximately 3–4 h, a 4-week wash-out period was judged to be sufficient.

Finally, we addressed the possibility of unblinding due to exposure to both substances. While there is no way to completely avoid this issue, we chose a placebo with a similar gastrointestinal side-effect profile to the IMP: mannitol, a sugar alcohol, can cause gastrointestinal disturbances, without having any systemic effect as it does not leave the gastrointestinal tract [58].

Various explorative outcomes have been included in order to be able to identify some of the potential protective mechanisms of exogenously induced ketosis in migraine. In addition, we are hoping this might help us distinguish responders and non-responders on both a phenotypical as well as physiological level.

